
As empirical assumptions for the interplay between depression and loneliness in the inpatient and follow-up depression therapy are rare, we decided to set a change of 2 points in the MADRS per 1 SD of loneliness (3-Item UCLA Loneliness Scale) as the minimum meaningful association that shall be detected via the interaction (baseline x change) over the inpatient and post-treatment course. The model tested baseline loneliness and change in loneliness with at least 1.75 points MADRS as we have no empirical assumptions about which association is more significant for this setting, but we have a theoretical assumption that these single associations are less significant than their interaction. An omnibus likelihood ratio test will evaluate these assumptions in a single model, followed by Holm-Bonferroni corrected single tests to evaluate these three assumptions. This step will also evaluate the direction of effects and theoretical plausibility (more loneliness at baseline and less change in loneliness shall predict higher depressive symptom severity). The primary analysis of the linear mixed model includes all three measurement points as a categorial factor. Potential time- effects will serve as covariates in this model and will be reported exploratory with no influence on sample size calculation. Studies examining the clinical course of inpatient depression treatment measured with the MADRS report partly comparable values of MADRS at baseline (≈ 30 points) (62–64) and discharge, though findings remain heterogeneous (65, 66). Model assumptions for this sample size calculation were therefore based on plausible clinical values: T0 = 30, T1 = 16, T2 = 15 MADRS points, with a constant standard deviation of *SD* = 8 across all time points. Between-person differences in depression symptom severity (MADRS) were considered with fixed and random slopes, and ICC was set at .50. Power simulation involved assumptions of approximately 5% missing completely at random (MCAR) and 10% missing at random dropout at T2 (MAR). Sample size estimation was performed with R using the following packages: lme4, lmerTest, MASS and tidyr. The simulation for the overall model yielded a statistical power of ≥ 80% for all three assumptions at *n* = 172 with 15% combined dropout rate (MCAR, MAR), resulting in a total of *n* = 199. The number of simulations was 500 (nsim = 500) at a significance level of *α* = 0.05 for the omnibus likelihood-ratio test, with Holm-Bonferroni corrected single hypothesis tests. As depression can lead to cognitive distortion, correlations between loneliness and depression might be dependent on the measurement point, and given the insufficient clinical validation of the loneliness measures, it remains unclear whether the assumptions of a normal distribution and the assumed level of measurement adequately describe the interplay between depression and loneliness. Additional statistical methods are employed in an explorative and descriptive manner (generalized linear mixed-effects model and mixed analysis of variance). Power-analysis for mixed ANOVA using G*Power Version 3.1.9.7, with categorical groups of ‘high’ and ‘low’ loneliness (median-split) when considering an α error of 0.05, a power of 0.9 (1-β error probability) and a correlation value among repeated measures of 0.5 for the group’s results an estimated sample size of *n* = 36 participants assuming a medium effect size (*f* = 0.25), and *n* = 214 participants assuming a small effect size (*f* = 0.10).

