### Statistical analysis

2.6

To perform the statistical analysis, IBM SPSS Statistics Version 29 (96) and R (97) are used. To address the primary objective of this study, which is to examine the clinical relevance of the interplay between loneliness and depression in an inpatient and post-inpatient treatment setting, a set of statistical approaches is employed. To address the primary hypothesis, a linear mixed model with likelihood ratio test will be conducted to test against the null hypothesis that baseline loneliness, change in loneliness or their interaction have no additional association with the symptom severity in the course of depression (T0, T1, T2). In the primary linear mixed-effects model, depressive symptom severity (MADRS) is modeled across the three main assessment points (T0 = admission, T1 = discharge, T2 = three-month follow-up), with time entered as a categorical factor. Baseline loneliness at T0 (applied to T0, T1, and T2), the change in loneliness from admission to discharge (applied to T1 and T2), and their interaction (baseline × change) are entered as fixed effects, alongside random intercepts and random slopes capturing individual differences in symptom level and course. Because the length of inpatient stay differs between participants, the individual inpatient treatment duration (days from admission to discharge) is included as a time-related covariate rather than assuming a fixed interval between T0 and T1. The biweekly interim assessments are not part of the primary model and are reserved for the exploratory within-/between-person trajectory analyses described below. The primary test is an omnibus likelihood-ratio test of the null hypothesis that baseline loneliness, change in loneliness, and their interaction jointly show no association with the course of depressive symptom severity; only if this omnibus test is significant are the three individual coefficients examined, with Holm–Bonferroni correction. The formal model specification and the complete list of covariates are provided in the **Supplementary Material** (Section 4 and **Supplementary Table S1**). All models will be controlled for time-effects (e.g., length of inpatient treatment duration), measures obtained at the same timepoint (e.g. explorative analysis of measurement specific associations of loneliness and depression), recruitment site, gender and age and will be tested for further covariates such as social anxiety and social support. The primary analysis sample will include all participants who completed T0 and T1 depression severity measures (MADRS) and loneliness measures (3-Item UCLA). For each questionnaire, missing individual data points are imputed using person-mean imputation, provided that no more than 20% of the data is missing. Participants with an inpatient stay shorter than seven days (post-enrollment exclusion criterion) are not part of the primary analysis set, since no discharge assessment (T1) is obtained for them; where baseline (T0) data are available, they are retained in the sensitivity analyses of all available data. The extent and pattern of missing values will be described for all inference statistical analysis. Given that dropout is likely associated not only with observed characteristics (MAR) but also with unobserved post-discharge symptom severity (MNAR), sensitivity analyses will include pattern-mixture models or selection models to evaluate the robustness of primary findings under MNAR assumptions. As a pragmatic benchmark, a worst-case analysis will be performed assuming that all dropouts at T2 experienced no improvement (last observation carried forward) or deterioration (fixed offset of +5 MADRS points).

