Secondary outcomes (quality of life, suicidality, social support and others) and biosamples will be analyzed exploratively and reported descriptively. To account for multiple testing in exploratory analysis, p-values will be adjusted using the Benjamini-Hochberg false discovery rate (FDR) procedure. To evaluate prognostic sensitivity and specificity of loneliness measures loneliness at the beginning of inpatient treatment and at discharge, cutoff values for loneliness scores (with 3-Item UCLA and 6-Item DJGLS Loneliness Scales being considered separately) are assessed exploratory by using ROC analysis. The severity of depression symptoms serves as reference standard for predicting response, which is defined as ≥ 50% reduction in MADRS scores from baseline (T0) to discharge (T1), and depression symptom severity measured with MADRS at T2 serves as reference standard for predicting relapse (defined as one or both of the following conditions: ≥ 10 MADRS points more from discharge to follow-up or ≥ 22 MADRS points at follow-up measurement), respectively. The exploratory ROC results are strongly sample-dependent. Because the cutoff values are derived from the present sample, their predictive value and transferability are markedly limited; the ROC analysis should therefore be regarded only as a first attempt at course- and risk-stratification, the validity of which would need to be confirmed in independent samples. A detailed descriptive presentation of all the measurement time points and all variables assessed will be performed, as well as an exploratory analysis using (generalized) linear mixed models.

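### The worst-case dropout analysis is not a worst case for the loneliness coefficients: a uniform offset can move them either way, depending on who drops out

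*Protocol article*

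**What the plan says.** All of this stands in the Protocol article.

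- **Statistical analysis, expected dropout.** The section accepts that "dropout is likely associated not only with observed characteristics (MAR) but also with unobserved post-discharge symptom severity (MNAR").
- **Statistical analysis, main response to it.** It states that "sensitivity analyses will include pattern-mixture models or selection models to evaluate the robustness of primary findings under MNAR assumptions".
- **Statistical analysis, the benchmark.** The next sentence reads "As a pragmatic benchmark, a worst-case analysis will be performed", and the rule for it is "assuming that all dropouts at T2 experienced no improvement (last observation carried forward) or deterioration (fixed offset of +5 MADRS points"). The text does not say whether the 5 points are added to the discharge score or to an expected T2 score. The offset is the same for every dropout.
- **Statistical analysis, what is tested.** The primary test is a joint likelihood-ratio test of three coefficients. Baseline loneliness acts at T0, T1 and T2, and change in loneliness at T1 and T2. The third is their interaction. The analysis set requires T0 and T1, so the last MADRS of a T2 dropout is the discharge score.
- **Statistical analysis, relapse.** For the exploratory ROC work, relapse means "≥ 10 MADRS points more from discharge to follow-up or ≥ 22 MADRS points at follow-up measurement".
- **Sample size consideration.** The assumed means are "T0 = 30, T1 = 16, T2 = 15 MADRS points", "with a constant standard deviation of *SD* = 8 across all time points". The smallest effects to be detected are 1.75 points for each loneliness main term and 2 points for the interaction.

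**The concern.** A reader takes an analysis labelled worst-case as a bound: if the result survives it, dropout cannot explain the result. That reading fails here for two reasons.

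First, the scenario is mild on average by the plan's own yardsticks. Carrying discharge forward almost reproduces the expected follow-up mean, and the 5-point rise is half the rise that the plan itself counts as relapse.

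Second, and more important, the primary test asks how MADRS varies with loneliness. An equal offset for all dropouts is pessimistic for the mean, but its effect on a slope depends on how dropout is distributed over loneliness. If lonelier patients are lost more often, the benchmark adds points mainly at the lonely end and steepens the association under test. It would then make a positive finding look firmer while being described as its hardest test.

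**Working it through.** The plan reports no result for this benchmark, so there is no figure to reproduce. The check has three steps.

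**1. Where the scenarios sit on the plan's scale** (means 30, 16, 15; SD 8)

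- Discharge carried forward: 16. Gap to the expected T2 mean: 16 − 15 = 1 point, or 1/8 = 0.125 SD.
- Offset added to discharge: 16 + 5 = 21. Offset added to the expected T2 value: 15 + 5 = 20. Both are below 22.
- Rise from discharge when the offset is added to discharge: 5, against the 10-point criterion. No dropout can meet that criterion under this reading.
- Share at 22 or above, normal distribution: mean 21, P(Z ≥ 1/8) = 0.45; mean 20, P(Z ≥ 2/8) = 0.40; planned T2 mean 15, P(Z ≥ 7/8) = 0.19.

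These figures assume that dropouts have the overall discharge mean. If theirs is 17, adding 5 gives exactly 22. At 10% dropout, an odds ratio of about 1.15 per SD of discharge MADRS is enough for that.

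**2. Effect of the offset on the slope at T2 alone**

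For dropout proportion p and odds ratio OR per SD of loneliness, the shift is approximately 5 × p(1 − p) × ln(OR).

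- p = 0.10, OR 1.5: 5 × 0.09 × 0.405 = 0.18
- p = 0.30, OR 1.5: 5 × 0.21 × 0.405 = 0.43
- p = 0.30, OR 2.0: 5 × 0.21 × 0.693 = 0.73

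**3. Effect on the coefficients that are tested**

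The tested coefficients pool visits, so a change at T2 only is diluted to roughly one third for baseline loneliness (three visits) and one half for change (two visits). Simulation with n = 199, SD 8, "ICC was set at .50" and effects 1.75, 1.75 and 2 agrees. My assumptions are no random slopes, uncorrelated loneliness terms, dropout following one loneliness term at a time, and change coded so that higher means lonelier. The shift shown is from adding 5 to the carried-forward score.

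| Dropout, OR per SD | T2-only ÷ 3 | Baseline, simulated | T2-only ÷ 2 | Change, simulated |
|---|---|---|---|---|
| 10%, 1.5 | 0.06 | 0.06 | 0.09 | 0.09 |
| 30%, 1.5 | 0.14 | 0.13–0.14 | 0.21 | 0.21 |
| 30%, 2.0 | 0.24 | 0.21–0.23 | 0.36 | 0.33–0.34 |

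Against 1.75: 0.06/1.75 = 3% and 0.23/1.75 = 13% for baseline; 0.09/1.75 = 5% and 0.34/1.75 = 19% for change.

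**Direction.** A harsher set of simulations used about 16% dropout and log-odds of 1 per SD, with results compared against a missing-at-random analysis:

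- Lonelier patients drop out more: baseline coefficient 1.73 to 1.95.
- Less lonely patients drop out more: 1.77 to 1.55.
- Dropout unrelated to loneliness: no movement.
- Lonelier patients drop out more, but less lonely dropouts get +5 and lonelier ones −5: 1.73 to 1.53.

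The upward shift applies to the term that dropout follows. When the two loneliness terms are correlated, the others can fall: at 29% dropout following baseline, baseline went from 1.75 to 2.07 while change went from 1.74 to 1.63.

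With no true association and lonelier patients dropping out more, joint rejection rose from 5.5% to 10.9%. Part of that is not the offset: carrying forward alone gave 7.9%, because it alters the covariance that the simulation held fixed.

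**The case against.** The strongest defence is that this run is only a benchmark. The job of testing robustness to informative dropout goes to pattern-mixture or selection models, and delta-adjusted imputation is itself a pattern-mixture method. A reader might infer that the plan has no real analysis for such dropout. The document does not support that, and this limits how serious the point is.

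The scenario is also not trivial. The share at 22 or above would go from 19% at the planned T2 mean to 40–45%. The relapse definition is an individual one from the exploratory ROC work, to which the benchmark is not tied, and the 1-point margin below 22 closes if dropouts average 17 at discharge.

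A reader might further infer that the benchmark can never overturn a positive result. That is wrong: the coefficient falls when less lonely patients drop out more, and the document states no relation between loneliness and dropout. Nor may the T2-only shifts of 0.18 to 0.73 be read against the 1.75-point effect, because the tested coefficients pool visits. Finally, the 30% rate comes from the recruitment feasibility argument. The power simulation used 10% missing-at-random dropout at T2 and 15% combined.

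What remains is the label, the missing reference value and the uniform offset. Naming the models without an offset or direction does not cure these: the benchmark is the only scenario with stated values, and its label invites reading it as a bound.

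**Conclusion.** The point holds in limited form. The stated rule is not a worst case for the primary test. It is mild on the plan's own means, and its effect on the tested coefficients has no fixed sign.

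The likely size is modest: about 0.06–0.23 MADRS points per SD for baseline loneliness and 0.09–0.34 for change. These ranges rest on assumed odds ratios of 1.5–2.0 per SD and dropout of 10–30%. The upper ends need the 30% feasibility rate. At the plan's combined 15%, the same shortcut gives 5 × 0.1275 × 0.405 = 0.26 to 5 × 0.1275 × 0.693 = 0.44 at T2, hence about 0.09–0.15 for baseline and 0.13–0.22 for change.

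Shifts of this size would rarely decide a result at the planned effects. They matter more if the true association is small, and they matter for what the check can be said to show. The plan should be changed, but the primary analysis is not undermined.

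**What to change.** 1. Rename the benchmark a fixed-offset scenario, and describe carrying discharge forward as no change since discharge.
2. State the value to which the 5 points are added.
3. Within the planned pattern-mixture analysis, specify a delta-adjusted multiple-imputation tipping-point analysis. Let the T2 offset run from 0 to at least +10, the plan's own relapse rise, and let it differ by loneliness. Include the adverse case, in which less lonely dropouts fare worse and lonelier dropouts better.
4. Report the offset at which the joint test is no longer significant.

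This needs some wording and a little more analysis work, and no additional data. It should be fixed before outcome data are examined.

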The primary hypothesis states that loneliness (3-Item UCLA Loneliness Scale) at admission, the change in loneliness from admission to discharge, and their interaction (admission x change in loneliness) will significantly predict depressive symptom severity, assessed using the Montgomery–Åsberg Depression Rating Scale (MADRS), in a linear mixed-effects model, tested using an omnibus likelihood ratio test (*α* = .05). As depression is our main outcome variable, we will also address this hypothesis for self-report data, measured with the Patient Health Questionnaire (PHQ-9). The loneliness scores of the 6-Item De Jong Gierveld Loneliness Scale will serve for sensitivity analysis to examine the measurement robustness and construct validity. A more detailed but exploratory analysis of the fixed and random effects and time-varying loneliness and depression within the inpatient and follow-up treatment period will be explored with linear mixed model analysis to 1) examine whether loneliness has a role in the inpatient therapy effect on depression symptom severity and its maintenance after discharge, 2) investigate the clinical relevance of chronic loneliness, and 3) describe the bidirectional relationship between loneliness and depression at all measures. To evaluate the prognostic value of baseline loneliness (3-Item UCLA Loneliness Scale) to predict response at discharge (≥ 50% reduction in MADRS) and the prognostic utility of loneliness at discharge to predict relapse (≥ 10 MADRS points more from discharge to follow-up or ≥ 22 MADRS points at follow-up), receiver operating characteristics (ROC) will be determined and reported in an exploratory fashion. Along with the main objective to investigate the clinical relevance of loneliness and depression, we will test several exploratory hypotheses. Since the duration of inpatient treatment has implications for the allocation of healthcare resources, we will test whether loneliness at admission and change in loneliness from admission to discharge are significant predictors of inpatient length of stay after adjusting for covariates. The secondary objective of the study is to identify the biopsychosocial processes that shape the interaction between loneliness and clinical depression. To this end, statistical analyses of additional clinically relevant outcomes (such as quality of life and suicidality) as well as interactional effects of potentially shared psychosocial mechanisms (including social support, social network, comorbidities, general health and physical activity) will be conducted. Exploratory analysis of blood, saliva and stool markers including metabolic, hormonal, immunological, and neurotrophic factors as well as microbiome diversity will deepen the understanding of pathophysiological processes. We hypothesize that more depressed and more lonely people will have the most unfavorable metabolic profile in blood markers (Low-Density-Lipoprotein, HbA1c), higher levels of inflammation or cellular stress (sphingolipid metabolism) and less neuroplasticity (BDNF). In terms of saliva pattern markers, we assume a higher stress response (cortisol, α-amylase activity) in individuals with more severe depression and loneliness. For stool markers, it is hypothesized that more depressed and lonely people have a less diverse stool microbiome (alpha-diversity). We hypothesize the changes in biomarker profile from baseline to discharge from clinic and baseline to follow-up to be associated with changes in depression severity and changes in loneliness experience.

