
Given that the study design does not permit definitive causal conclusions to be determined about the direction of all fixed and random effects, the findings are still expected to provide valuable insights and relevant implications. In particular, the following insights can be obtained (1): a report on whether patients with different levels of loneliness receive equal benefits from inpatient multimodal depression treatment; (2) insights into changes in loneliness during and after depression treatment; (3) important preliminary findings regarding the shared and distinct biopsychosocial mechanisms underlying loneliness and depression; and (4) the relationship of loneliness and depression on to secondary outcomes, including quality of life and suicidality.

Should the primary hypotheses be confirmed — that is, if baseline loneliness, change in loneliness or their interaction is significantly associated with the level of depressive symptom severity across the treatment course — this may carry implications for clinical practice. First, a brief loneliness screening (requiring less than two minutes using the 3-Item UCLA Loneliness Scale) might be considered for integration into routine psychiatric admission assessments, as it may enable clinicians to identify patients at risk for poorer treatment outcomes early in the treatment process — though randomized controlled studies would be needed to determine whether such screening translates into improved clinical outcomes. Second, the exploratory distinction between more situational and more enduring aspects — examined here only descriptively and without a validated state-trait measure — may, if associated with the course of depressive symptom severity, generate hypotheses for future interventional studies. Such studies could evaluate whether loneliness-focused components (e.g., cognitive restructuring of maladaptive social cognitions or facilitated social re-engagement during the transition from inpatient to outpatient care) add value to multimodal depression treatment. Any inference about modifiability would require an interventional design and lies beyond the scope of the present observational study. Third, the finding that loneliness at discharge predicts relapse would underscore the importance of addressing social connectedness as part of discharge planning and aftercare, a dimension that is currently underrepresented in German psychiatric treatment guidelines.

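### The relapse outcome sets no condition on the discharge score, so about 40% of counted relapses would be patients already at or above 22 MADRS points at discharge

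*Protocol article*

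**What the plan says.** The rule appears twice. In the Introduction, the aim is to assess "the prognostic utility of loneliness at discharge to predict relapse", with relapse given as "≥ 10 MADRS points more from discharge to follow-up or ≥ 22 MADRS points at follow-up". The Statistical analysis section repeats the two thresholds, "≥ 10 MADRS points more from discharge to follow-up or ≥ 22 MADRS points at follow-up measurement", and makes the combination explicit: relapse is "defined as one or both of the following conditions". Response, a halving of the MADRS from admission to discharge, is defined beside it as a separate outcome and is not a precondition for relapse. Nothing else in the article limits the relapse ROC to patients who had improved or were below a given score at discharge.

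The planning values are in Sample size consideration: "T0 = 30, T1 = 16, T2 = 15 MADRS points", "with a constant standard deviation of *SD* = 8 across all time points", and an ICC of .50. The Discussion says what a positive result would be used for: "the finding that loneliness at discharge predicts relapse would underscore the importance of addressing social connectedness" in discharge planning and aftercare.

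**The concern.** Relapse implies a return of symptoms after improvement. The second condition looks only at follow-up, so a patient who left hospital at 28 and came back at 23 is a case although the score fell by 5 points. The outcome mixes two groups: patients who worsened after discharge, and patients who were above the threshold at discharge and stayed there.

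This matters because the predictor, loneliness at discharge, is measured at the same visit as the discharge MADRS. If the two are correlated at that visit, loneliness can appear to predict relapse merely because it marks patients who were still depressed when they left. The Discussion would attach a statement about aftercare to that result, and such a statement needs an outcome that separates new worsening from persistence.

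**Working it through.** The article states no relapse proportion, so there is no figure of its own to reproduce. The check projects the rule onto the planning values.

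**Inputs from Sample size consideration.** Mean MADRS 16 at discharge (T1) and 15 at follow-up (T2); SD 8; n = 172, used here only as a convenient number of patients with T2 data.

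**Assumptions.** (T1, T2) is bivariate normal. The T1–T2 correlation is taken as the ICC of .50. Because random slopes are also named without variances, .3 to .7 is examined. Results are given for continuous scores and for scores rounded to integers and limited to 0–60.

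**Step 1: already at 22 or more at discharge.** Continuous: (22 − 16)/8 = 0.75, upper tail 22.7%. Integer scores: (21.5 − 16)/8 = 0.6875, upper tail 24.6%.

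**Step 2: share of relapses already at 22 or more at discharge.** A patient with T1 ≥ 22 who meets either condition necessarily has T2 ≥ 22, so

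share = P(T1 ≥ 22 and T2 ≥ 22) / P(T2 − T1 ≥ 10 or T2 ≥ 22).

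At correlation .5 this is 9.2% / 23.2% = 39.6% (continuous) or 10.4% / 24.9% = 41.8% (integer).

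**Step 3: share of relapses with no worsening (T2 ≤ T1).** These patients must have T2 ≥ 22 and hence T1 ≥ 22, so they are a subset of step 2.

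| T1–T2 correlation | Relapse rate (integer) | T1 ≥ 22 among relapses, continuous / integer | T2 ≤ T1 among relapses (integer) |
|---|---|---|---|
| .3 | 26.3% | 28.6% / 30.7% | 17% |
| .5 | 24.9% | 39.6% / 41.8% | 24% |
| .7 | 22.9% | 56.2% / 57.6% | 34% |

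Changing the SD from 6 to 10 at correlation .5 moves the continuous share only from 37% to 41%.

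**Step 4: effect on the ROC.** Suppose loneliness at discharge correlates .3 to .5 with T1 MADRS and is independent of T2 MADRS given T1, so that it carries no prognostic information beyond the discharge score. Both parts are assumptions. The nearest figure in the article is a cross-sectional r of about .50 from non-clinical samples.

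| T1–T2 correlation | AUC as defined (r = .3 to .5) | AUC among T1 < 22 (r = .5) |
|---|---|---|
| .3 | about .50 | .47 |
| .5 | .54 to .56 | .50 |
| .7 | .58 to .64 | .54 |

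**Step 5: events per 172 patients with T2, correlation .5, integer scores.** All relapses: 0.249 × 172 ≈ 43. Relapses with T1 < 22: 0.754 × 0.192 × 172 ≈ 25. The other 18 or so were at 22 or more at both visits.

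**The case against.** The strongest reply is that little hangs on this outcome. The relapse ROC is labelled exploratory, lies outside the omnibus test, the Holm-corrected coefficients and the sample size simulation, and is described as a first attempt that needs confirmation in independent samples. The Discussion sentence on aftercare is conditional. It also warns that severe depression may colour loneliness ratings, and the plan includes continuous analyses of within- and between-person change. All of this stands and limits the severity. It does not answer the point: the ROC caveats concern optimism and transferability, and an independent sample scored by the same rule would reproduce the misclassification.

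Three stronger readings are tempting, and the documents do not support them.

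- A reader might infer that the ROC is necessarily pushed above .5. It is not: at a T1–T2 correlation of .3 there is no inflation. At .5 it is .04 to .06, against a standard error of about .05 with some 42 events in 170 patients.
- A reader might describe the scenario in step 4 as loneliness unrelated to later change. It is not that: through regression to the mean, loneliness then correlates about −.25 with T2 − T1 (r = .5, T1–T2 correlation .5).
- A reader might say that 40% of relapses never recovered. The calculation shows only that they were at 22 or more at discharge. A patient going from 46 to 23 meets the protocol's response definition and is still above that line. About one percentage point of the 40% also rises by 10 or more after discharge, which is real worsening.

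**Conclusion.** The point holds as a defect in the definition of an exploratory outcome. The missing discharge condition is plain in both statements of the rule and does not depend on any calculation. Its size is a projection: about 40% of counted relapses already at or above the protocol's own 22-point threshold at discharge (roughly 30% to 58% for T1–T2 correlations of .3 to .7), and about 24% (17% to 34%) with no worsening, given normality and the planning means and SD. The consequence is that the ROC partly reflects the concurrent association of loneliness with depression persisting at discharge. Whether this appreciably inflates the AUC cannot be settled from the documents, because it depends on how stable scores are after discharge and on an unknown correlation between loneliness and the discharge MADRS. It is worth correcting before analysis because it changes what the relapse ROC can show. A reader might infer that the primary hypothesis test is compromised, but that test models the MADRS itself and does not use the relapse outcome.

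**What to change.** Keep both thresholds as stated, and add one sentence to the Statistical analysis section (and its counterpart in the Introduction) defining who is at risk of relapse at discharge. Two candidates already exist in the protocol: patients below its 22-point threshold at T1, or T1 responders by its own response definition. The choice is for the investigators. Run the relapse ROC in that set. Report patients at 22 or more at both visits separately as persistent depression, noting any who also rose by 10 or more. Also report whether loneliness at discharge adds to the T1 MADRS as a predictor. This is needed even in the restricted set, where the AUC under the step 4 assumptions is still .54 at a T1–T2 correlation of .7.

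No new data are needed. With the below-22 set, the price is fewer events, about 25 rather than 43 per 172 patients with T2 data, and so wider intervals. A patient moving from 21 to 22 would still count as a relapse, which follows from keeping the stated threshold.
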